## Abstract

**Background:**

Cancer-related fatigue (CRF) is a debilitating condition which commonly affects cancer survivors. The management of CRF remains a challenge due to the lack of effective pharmacological interventions. Traditional Chinese medicine (TCM) could be a potential therapeutic option for CRF. The modified Xiang Bei Yang Rong Tang (XBYRT) is a TCM herbal decoction, formulated to improve fatigue symptoms in cancer survivors. This clinical trial aims to evaluate the efficacy and safety of XBYRT in improving CRF and quality of life (QOL) of cancer survivors.

**Methods:**

This is a single centre, randomized, double-blind, placebo-controlled, parallel trial. Eighty cancer survivors will be recruited and randomized to receive the XBYRT or placebo decoction, in a ratio of 1:1. Participants will consume the XBYRT/placebo decoction daily for 8 weeks and undergo assessments at baseline and 4, 8 and 10 weeks after baseline. The participants will be assessed for patient-reported outcomes (PRO), blood biomarkers and adverse events at each time point. The primary outcome is the overall health and QOL status, at 8 weeks follow-up. The secondary outcomes are the effects of XBYRT on fatigue levels, cancer-related cognitive impairment and QOL, as assessed by PRO. The incidence of adverse events and the effects of the XBYRT decoction on blood biomarkers associated with CRF will also be evaluated.

**Discussion:**

Efficacy and safety outcomes from this trial will provide important clinical data to guide future large-scale randomized controlled trials, and the evaluation of the objective blood biomarkers can help to delineate the biological mechanisms of CRF.

**Trial registration number:**

ClinicalTrials.govNCT04104113. Registered on 26 September 2019

## Introduction

Advances in diagnosis and treatment have resulted in better survival rates and an increase in the number of cancer survivors [1]. Cancer survivors often experience a wide range of radiotherapy or chemotherapy-induced side effects which may persist for years even after the cessation of treatment. Cancer-related fatigue (CRF) has been reported as the most distressing symptom experienced by cancer patients and can have debilitating physical, emotional and cognitive effects which negatively impact the patients’ quality of life (QOL) [2, 3]. Up to 45% of cancer patients suffer from clinically significant CRF during treatment, and approximately 29% still experience fatigue after the completion of treatment [4].

The pathophysiology and mechanisms leading to CRF and the factors causing persistent fatigue in cancer survivors are not well understood, despite it being a highly prevalent symptom in cancer patients and survivors. This is because the pathophysiology underlying CRF is complex involving psychological, physical and biological factors. One of the postulated biological factors contributing to the development of CRF is inflammation from immune activation caused by cancer and its treatment. Dysregulation of circulating inflammatory markers and cytokines such as interleukin-1 receptor antagonist (IL-1RA), interleukin-6 (IL-6) and C-reactive protein (CRP) has been reported in cancer patients and survivors experiencing CRF [5–8]. Chemotherapy, along with a pro-inflammatory environment, induces a number of downstream toxic effects, including an increase in reactive oxygen species which can result in mitochondrial impairment [9–11]. Mitochondrial dysfunction has been implicated as one of the possible biological factors of chronic fatigue syndrome and CRF [12–14].

In Asia, many cancer patients seek complementary and alternative medicine (CAM) to manage their cancer-related symptoms or improve their general health, and one of the most commonly used CAM is traditional Chinese medicine (TCM) [15–17]. According to the TCM concept, CRF is characterized by the deficiency of qi, the vital energy of the body, along with blood deficiency [18]. Chemotherapy and radiotherapy deplete both qi and blood by indiscriminately destroying growing cells, damaging the bone marrow and weakening the body. Qi deficiency was found to be associated with CRF and a poorer QOL in cancer patients [18, 19]. In addition, a few studies looking at various TCM decoctions have shown effectiveness in improving fatigue levels in cancer patients [20–23]. However, the efficacy of TCM is not backed with robust clinical evidence and safety data as most of these studies suffer from the lack of adequate control and blinding which might introduce bias in the results. Therefore, more well-designed randomized controlled clinical trials are needed to evaluate the efficacy and safety of TCM in treating CRF.

The TCM formula for this randomized controlled trial is a modification of Xiang Bei Yang Rong Tang (香贝养荣汤). Xiang Bei Yang Rong Tang (XBYRT) was described in the ancient TCM text “Yi Zong Jin Jian” volume 64 and is used for nourishing qi and blood [24]. The 15 herbal components in the modified XBYRT formula were selected based on their ability to augment qi, nourish the blood, improve appetite and calm the mind which can help to alleviate CRF symptoms in cancer survivors.

The primary objective of this trial is to evaluate the efficacy of XBYRT in improving the overall health status and QOL in a cohort of cancer survivors, assessed using the global health status of the European Organization for Research and Treatment of Cancer Quality of Life Questionnaire (EORTC QLQ-C30), at 8 weeks follow-up. The secondary objectives of this trial are to determine the effects of XBYRT on fatigue levels, cancer-related cognitive impairment and QOL. In addition, the safety outcomes associated with XBYRT and the impact of the TCM decoction on biomarkers associated with CRF will be evaluated.

## Methods

### Study design

This is a single-centre randomized, double-blind, placebo-controlled, parallel trial, and the protocol for this trial has been prepared in accordance with the Standard Protocol Items: Recommendations for Interventional Trials (SPIRIT)–TCM extension statement 2018 (Additional file 1) [25]. This study protocol has received ethical approval from the Centralised Institutional Review Board (2019/2135) and is registered in ClinicalTrials.gov (NCT04104113). Written informed consent will be obtained from all study participants. A total of 80 cancer survivors will be enrolled from the outpatient oncology clinics at the National Cancer Centre Singapore (NCCS), and the recruitment and follow-up period for this trial will be from October 2019 to December 2021.

### Participants

The target study participants are cancer survivors who complain of fatigue and will be recruited through referrals from oncologists. Cancer survivors will be screened for fatigue using a single item, where patients will be asked to rate their fatigue on a scale of 0 to 10 over the past 7 days. A score of 0 means no fatigue, and mild fatigue is indicated as a score of 1 to 3, moderate fatigue as 4 to 6 and severe fatigue as 7 to 10 [26]. Patients with ratings ≥ 4 are considered as experiencing significant fatigue. Potential participants will also be screened by certified TCM physicians based on TCM syndrome differentiation. The eligibility criteria are as follows:
Age ≥ 21 yearsClinically diagnosed cancer (stages I–III)Completed surgery/chemotherapy/radiotherapy for at least 1 monthAt least 1 month after starting on aromatase inhibitors or ovarian suppression for breast cancer survivorsNot expected to receive surgery/chemotherapy/radiotherapy for the next 10 weeksFatigue screening score ≥ 4 for the past 7 daysLife expectancy ≥ 3 monthsPatients who satisfy TCM syndrome differentiation as qi and blood deficiency: experience 2 major symptoms coupled with typical tongue and pulse conditions; 2 major symptoms and 1 possible symptom coupled with tongue and pulse conditions; and 1 major symptom and at least 2 possible symptoms coupled with tongue and pulse conditionsAble to read and understand English or Mandarin

The exclusion criteria are as follows:
Cancer recurrence and/or metastasis.Untreated co-morbidities causing fatigue (e.g. severe anaemia, thyroid disorder).On medications that cause fatigue (e.g. beta blockers).Patients on warfarin.Cancer survivors receiving adjuvant therapy during the study period. Aromatase inhibitors and anti-human epidermal growth factor receptor 2 (HER2) monoclonal antibodies are acceptable.Receiving or planning to receive treatment from other TCM practitioners during the study period.Breastfeeding or intending to conceive/get pregnant during the study treatment period.Patients who present with yin deficiency and excess syndromes (e.g. phlegm-dampness, blood stasis, toxic heat and qi stagnation).

### Intervention

Study participants will take either the assigned XBYRT or placebo which is prepared as granules once daily for a duration of 8 weeks. Participants are required to dissolve the XBYRT or placebo granules in a cup of hot water and consume the decoction. During the study period, participants will be asked to refrain from taking other supplements or herbal medicines.

The experimental group will be given the XBYRT granules. The formulation, the TCM indication and the daily dosage of the XBYRT are displayed in Table 1. The study dosage is selected based on the safety and efficacy guidelines from the *Pharmacopoeia of the People’s Republic of China* and *General Eleventh Five-Year National Planning Textbook for Higher Education: Chinese Materia Medica* [27, 28]. The dosage indicated in Table 1 represents the amount of raw materials required for the extraction of the granules. The dried granules are extracted from the boiled aqueous concentrate of the raw materials. The final daily dosage consists of 24 g of extracted granules.

**Table 1 Tab1:** Formula and components of the modified Xiang Bei Yang Rong Tang decoction

Chinese name	Chinese name (Pinyin)	Scientific name	Dosage (g)	Purported effect
黄芪	Huang Qi	Radix Astragaliseu Hedysari	15	Augments qi and raises yang, augments defensive qi, consolidates the superficies, promotes drainage of pus and healing, facilitates water movement and reduces swelling
党参	Dang Shen	Radix Codonopsis Pilosulae	15	Tonifies the middle jiao, augments qi and generates fluids and blood
白术	Bai zhu	Rhizoma Atractylodis Macrocephalae	12	Augments qi, strengthens the spleen, dries dampness, promotes diuresis and stops sweating
茯苓	Fu Ling	Poria	15	Drains water, dissipates dampness, strengthens the spleen and calms the mind
白芍	Bai Shao	Radix Paeoniae Alba	15	Nourishes the blood, retains yin, soothes the liver and relieves pain, and stops excessive perspiration
枸杞子	Gou Qi zi	Fructus Lycii	12	Nourishes the liver and kidney, clears the eyes and moistens the lung
女贞子	Nü Zhen Zi	Fructus Ligustri Lucidi	12	Tonifies the liver and kidney, cools heat and clears the eye
车前子	Che Qian Zi	*Plantago asiatica*	12	Induces diuresis, drain dampness, improve vision and resolve phlegm
鸡内金	Ji Nei Jin	Endothelium Corneum Gigeriae Galli	10	Promotes digestion and invigorate spleen, arrest seminal emission and relieve enuresis
生麦芽	Sheng Mai Ya	*Hordeum vulgare* L.	15	Promotes digestion and invigorate spleen, stop lactation and release distension
益智仁	Yi Zhi Ren	Fructus Alpinia oxyphylla	10	Tonifies kidney yang, secure essence and reduce urination, warm spleen yang, improve appetite and reduce salivation
香附	Xiang Fu	Rhizoma Cyperi	10	Unblocks the liver and regulates qi, regulates menstruation and stops pain
远志	Yuan Zhi	Radix Polygalae	10	Stabilizes the heart and calms the mind, dissolves phlegm and opens orifices, and reduces abscesses and swelling
浙贝母	Zhe Bei Mu	Bulbus Fritillariae Thunbergii	10	Clears heat and resolves phlegm, disperses masses/abnormal growth and promotes the healing of carbuncles
土茯苓	Tu Fu Ling	Smilax glabra Roxb	15	Removes toxicity, excrete dampness and ease joint movement

The control group will receive a daily dosage containing 24 g of placebo granules. The placebo granules comprise of 5% of the herbal components, 95% maltodextrin, colourant and 0.002% denatonium benzoate as bitterant. This is to ensure that the placebo possesses the taste and smell of the herbal components. For this reason, it is a common practice in TCM trials to incorporate herbal components ranging from 5 to 10% in the placebo decoction, and this concentration is unlikely to exert a therapeutic effect [29, 30]. The placebo will be colour adjusted to match the XBYRT granules, and the packaging for the XBYRT and placebo granules will be similar in appearance. In order to encourage adherence to the study intervention, participants will be reminded to take their daily dosages and record their missed dosages.

Both the XBYRT and placebo granules will be manufactured by Kinhong Pte Ltd., Singapore, a Good Manufacturing Practices-certified manufacturer. A certificate of analysis containing the results on component identification, moisture content and the absence of heavy metal and microbial contamination will be available for each batch of XBYRT/placebo granules manufactured.

### Randomization, allocation concealment and blinding

Recruited participants will be randomized into the XBYRT or placebo treatment arm by block randomization at a 1:1 ratio, with a block size of 10. The consultant physicians, study team, trial pharmacists and study participants are blinded to the intervention to minimize potential bias. Randomization and blinding will be performed by a third party clinical trial service provider, Singapore Clinical Research Institute, using the sealed envelope method. Participants will collect the granules from the clinical trial pharmacy at NCCS based on their pre-assigned numbers.

### Sample size

In order to ensure that the sample size is adequately powered to estimate a reliable standard deviation (SD) for a phase III trial, Teare et al. has recommended to include at least 70 subjects (35 per arm) for estimating the SD for a continuous outcome [31]. Therefore, to account for a 10% dropout, a total sample size of 80 patients (rounded up from 78), with 40 participants on each arm, is required for this study.

### Assessments

Participants will be assessed at four time points: baseline and 4 weeks, 8 weeks and 10 weeks after baseline (Fig. 1). At the baseline visit, the participant’s demographics, medical history, cancer diagnosis and concomitant medications will be recorded in a standardized data collection form. The participants will be assessed for patient-reported outcomes (PRO) and objective blood biomarkers at each time point (Fig. 2). Participants will also be monitored for safety and adverse events (AE).

**Fig. 1 Fig1:**
[figure not shown]
Flow diagram of the study design and assessment time points

**Fig. 2 Fig2:**
[figure not shown]
SPIRIT figure for the enrolment, interventions and assessments of the study

#### Assessment of quality of life

The European Organisation for Research and Treatment of Cancer Quality of Life Questionnaire (EORTC-QLQ 30) is a self-administered questionnaire that measures the health-related QOL. The English and Chinese versions of this questionnaire have been validated in Singaporean cancer patients [32, 33]. It consists of 30 items across five functional domains (physical, role, cognitive, emotional and social), three symptom domains (fatigue, pain and nausea/vomiting), six individual items (dyspnea, insomnia, anorexia, diarrhoea, constipation and financial stability) and a global health status domain. All items are linearly transformed into a score ranging from 0 to 100. A higher score represents better functional status and health-related QOL in the functional and global health status domain while a higher score in the symptom domain or individual symptom item is interpreted as a worse extent of symptoms experienced by the patient.

#### Assessment of fatigue

The Multidimensional Fatigue Symptom Inventory-Short Form (MFSI-SF) is a multidimensional questionnaire for measuring fatigue in cancer patients. The English and Chinese versions of MFSI-SF have been validated in breast cancer patients in Singapore [34]. This 30-item questionnaire contains five subscales: general fatigue, physical fatigue, emotional fatigue, mental fatigue and vigour. Specific subscale scores are obtained by tabulating the item scores from each subscale. The MFSI-SF subscale scores can be combined to obtain an overall score. A higher score reflects a worse fatigue level.

#### Assessment of cognition

The Functional Assessment of Cancer Therapy-Cognitive Function (FACT-Cog) version 3 is used to assess subjective cognitive function. Both the English and Chinese versions of FACT-Cog have been validated in cancer patients in Singapore [35]. This questionnaire has 37 items containing assessments for six domains of cognition (memory, concentration, mental acuity, verbal ability, functional interference and multitasking) and two subscales for noticeability and impact on QOL. A global FACT-Cog score is derived from the total of the domain/subscale scores. Higher scores indicate better perceived cognitive abilities and QOL.

#### TCM symptom scoring

The TCM symptom scoring form is referenced from the combination of qi and blood deficiency from the National Standards of People Republic of China and details the method of pattern identification [36]. The form contains assessments for 9 major TCM symptoms and 7 possible TCM symptoms (Table 2). These symptoms are scored on an ordinal scale of absent, mild, moderate and severe. The scoring tool will be completed by the assessing TCM physician, and the patient’s pulse and tongue appearance will be assessed from the TCM’s perspective. Information collected from the questionnaire will be used to screen for inclusion and monitor the response of the participants towards the TCM decoction.

**Table 2 Tab2:** Major and possible symptoms assessed for TCM symptom scoring

Major symptoms	Possible symptoms
Shortness of breath	Spontaneous sweating
General fatigue	Reluctance to talk
Weakness	Insomnia
Pale or sallow complexion	Limb numbness
Dizziness, blurred vision	Scanty menstruation
Heart palpitation	Nausea, vomiting
Poor appetite	Weakness in defaecation
Abdominal distension after food	
Loose stools	

### Safety monitoring

Safety of study participants will be monitored at every time point assessment through blood tests evaluating organ functions such as liver and renal function tests, electrolyte level and full blood count. Participants will be asked to report any adverse effects experienced during the follow-up period which are graded according to the Common Terminology Criteria for Adverse Events (CTCAE) version 5 [37]. There are five grades in ascending order of severity, with grade 1 representing mild symptoms and grade 5 representing death. In order to monitor the adverse events (AEs) or serious adverse events (SAEs), an independent Data and Safety Monitoring Board (DSMB) review will convene for every 20 patients recruited for the trial. Therefore, there will be a total of three DSMB meetings for this trial. Analysis comparing the incidence of AEs based on the intervention group will be conducted at each DSMB review. The DSMB will make recommendations to the study team regarding the appropriate courses of action to address study safety issues which may arise during the trial. Unblinding to the study team is allowed only when the identification of the intervention arm is absolutely necessary for further management of the participant, for example, in the event of a SAE.

### Assessment of biomarkers

Blood samples from participants will be collected for biomarker assessments at all assessment time points.

#### Mitochondrial DNA content

The mitochondrial DNA (mtDNA) will be extracted from the buffy coat, and mtDNA content will be evaluated in relation to CRF. To measure mtDNA content, real-time quantitative polymerase chain reaction (PCR) will be performed using the Quantifast SYBR Green Master Mix from Qiagen along with the forward and reverse primers for Mito and β2 microglobulin (B2M). The Mito primer pair will amplify the ZFP28 zinc finger protein gene in mtDNA, while the B2M primer pair targets the beta-2-microglobulin gene in nuclear DNA (nDNA). The analysis will be performed in triplicates on 96-well plates, and target sequences will be amplified in a Biorad CFX96 Touch cycler. The average threshold cycle (Ct) values of nuclear DNA and mtDNA from each triplicate series are obtained, and the ΔCt method is applied (ΔCt = CtnDNA − CtmtDNA). The relative mtDNA copy number is derived from 2 × 2^ΔCt^, taking into account that nDNA is diploid.

#### Inflammatory cytokines

Plasma levels of inflammatory marker C-reactive protein (CRP) and cytokines TNF-α, IL-1β, IL-6 and IL-8 will be measured. The choice of cytokines is based on the findings of a systematic review which suggest that the development of CRF is influenced by immune dysregulation of which the aforementioned cytokines have been shown to contribute to worsening or persistent fatigue [8]. The cytokines of interest will be quantified using the highly sensitive multiplex immunoassay (Luminex®).

#### Oxidative stress markers

Plasma levels of malondialdehyde (MDA), superoxide dismutase (SOD) and glutathione peroxidase (GSH-Px) will be measured using commercially available assay kits.

### Outcomes

#### Primary outcome

The primary endpoint is the difference in global health status (GHS) score between the XBYRT interventional and placebo arms from baseline to 8 weeks after baseline. The GHS is a two-item domain from the EORTC-QLQ 30.

#### Secondary outcomes

Secondary outcomes are the changes in MFSI-SF and FACT-Cog total scores, including the subscale or domain scores between the XBYRT and placebo arms from baseline to 4, 8 and 10 weeks after baseline. Changes in the functional and symptom domain scoring of the EORTC QLQ-C30 from baseline will also be evaluated. Safety outcomes will be reported as the incidence of AEs or SAEs in study participants.

#### Biomarkers

Changes in circulating levels of inflammatory markers CRP, TNF-α, IL-1β, IL-6 and IL-8 from baseline to 4, 8 and 10 weeks after baseline will be compared between the XBYRT and placebo arms. Circulating oxidative stress markers, malondialdehyde (MDA), superoxide dismutase (SOD) and glutathione peroxidase (GPx), as well as mtDNA levels, will also be compared between the XBYRT and placebo arms for the aforementioned time points.

### Data management

The research data will be entered into a password-protected electronic database, and the entered data will be checked with the source documents to ensure data accuracy, by an independent study team member who is not in charge of data entry. The hard copy of study records or electronic study database will be kept in controlled access locations under lock and key. Investigators involved in this study will have access to the final dataset.

### Statistical analysis

The difference in GHS scores at 8 weeks after baseline between XBYRT intervention and placebo will be assessed using independent *t* test. To assess for the longitudinal effect of score changes over time, linear mixed models will be used to compare the outcomes between XBYRT intervention and placebo at the respective time points, adjusting for baseline values and clinically relevant factors. Individual-specific effects will be treated as random effects. Biomarker levels will also be evaluated using *t* tests and linear mixed models. The safety outcomes will be reported in proportions of patients experiencing AEs (% in terms of incidence) using the CTCAE v5.0 Criteria. Chi-square test will be used to evaluate the difference in severity (by grades) between the XBYRT intervention and placebo groups. An intention-to-treat (ITT) analysis approach will be adopted, and the data from all participants who are randomized and completed the trial without any major violation of the protocol will be analysed. Missing data will be treated as missing completely at random.

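### The primary endpoint is worded as a baseline-to-week-8 difference in GHS, but the test compares week 8 scores without using the baseline GHS; the two should be reconciled on one baseline-adjusted analysis

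*Protocol article*

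**What the plan says.** The Primary outcome section reads: "The primary endpoint is the difference in global health status (GHS) score between the XBYRT interventional and placebo arms from baseline to 8 weeks". The natural reading is a comparison of change.

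The Statistical analysis section opens differently: "The difference in GHS scores at 8 weeks after baseline between XBYRT intervention and placebo will be assessed using independent" t test. That compares week 8 values and has no baseline term.

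Two other places side with the week 8 value. The abstract states: "The primary outcome is the overall health and QOL status, at 8 weeks follow-up". The last paragraph of the Introduction also places the primary objective at the 8-week follow-up.

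Baseline GHS will be available. Under Assessments: "Participants will be assessed at four time points: baseline and 4 weeks, 8 weeks and 10 weeks after baseline", with patient-reported outcomes taken at each. After the t test, the Statistical analysis section adds linear mixed models for the longitudinal effect, "adjusting for baseline values and clinically relevant factors".

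**The concern.** Two things are at stake.

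The first is clarity. One section describes a change and another tests a week 8 value. Under randomization both have the same expected between-arm difference, but on one data set they give different estimates, standard errors and p-values. A reader of the results should not have to decide which was meant.

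The second is precision. GHS is measured on the same person before and after treatment, so the baseline score is likely to predict part of the week 8 score. An unadjusted comparison leaves that predictable part in the error term. In a trial of 80 with no stratification described, chance differences in baseline GHS then add noise that adjustment would remove.

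**Working it through.** **The plan's own figure.** The Sample size section relies on a source that "has recommended to include at least 70 subjects (35 per arm) for estimating the SD for a continuous outcome" and allows for 10% dropout. 70 / (1 − 0.10) = 77.8, so 78, rounded up to 80. This reproduces. With 40 per arm and 10% lost, 40 × 0.90 = 36 per arm are evaluable.

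**Assumptions, none given in the article.** True effect 0.5 SD; two-sided 5% level; equal SD at baseline and week 8 (set to 1); correlation ρ between baseline and week 8 GHS of 0.3, 0.5 or 0.7.

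**Effective SD of each analysis.**
- t test on week 8 scores: 1
- t test on change: √(2(1 − ρ))
- ANCOVA on baseline: √(1 − ρ²)

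**Power.** The noncentrality is (0.5 / SD) × √(36/2), referred to the noncentral t distribution with 70 degrees of freedom (69 for ANCOVA). For the week 8 t test it is 0.5 × 4.243 = 2.121, giving 55.3% power at any ρ.

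| ρ | Change: SD | Change: noncentrality | Change: power | ANCOVA: SD | ANCOVA: noncentrality | ANCOVA: power |
|---|---|---|---|---|---|---|
| 0.3 | √1.4 = 1.183 | 1.793 | 42.4% | √0.91 = 0.954 | 2.224 | 59.2% |
| 0.5 | √1.0 = 1.000 | 2.121 | 55.3% | √0.75 = 0.866 | 2.449 | 67.6% |
| 0.7 | √0.6 = 0.775 | 2.739 | 77.1% | √0.51 = 0.714 | 2.970 | 83.4% |

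**Gain of ANCOVA over the planned t test.** 59.2 − 55.3 = 3.9 points; 67.6 − 55.3 = 12.3 points; 83.4 − 55.3 = 28.1 points. To match ANCOVA with 36 per arm, the unadjusted test would need 36/0.91 = 39.6, 36/0.75 = 48 or 36/0.51 = 70.6 per arm.

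**Change against the alternatives.** Its variance 2(1 − ρ) is below 1 only when ρ exceeds 0.5, so below that it does worse than the week 8 t test. Against ANCOVA, 2(1 − ρ) − (1 − ρ²) = (1 − ρ)², which is never negative, so a change score never has the smaller variance.

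**Check by simulation.** With 35 per arm and 3,000 runs per ρ, power at ρ = 0.3, 0.5 and 0.7 was 53% to 55% for the t test, 40%, 56% and 76% for change, and 56%, 66% and 81% for ANCOVA. These are slightly lower, as expected with one fewer patient per arm and the baseline slope estimated from the data. The ordering is the same.

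**The case against.** The strongest defence is that the plan is sound as it stands. The abstract, the objective and the Statistical analysis section all point to the week 8 value, and only the Primary outcome section adds a baseline. Even there the word is difference, whereas the secondary outcomes and biomarkers are described as changes. This narrows the conflict to one sentence, but that sentence defines the primary endpoint, so it still needs reconciling.

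Four stronger readings are tempting, and the document supports none of them.

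- **That the t test is biased or invalid.** With 1:1 randomization it is unbiased and keeps its type I error. Chance baseline imbalance is already reflected in its standard error.
- **That the plan discards baseline GHS.** Only the t test leaves it unused; the mixed models adjust for baseline values.
- **That the plan offers three rival primary results.** No section names a test on change scores, and the mixed models are introduced for a separate, longitudinal purpose. Only the t test is attached specifically to week 8 GHS. It is true that the Statistical analysis section does not label it primary and that the mixed model also yields a week 8 contrast.
- **That the trial misses its intended power.** It states none. The sample size serves to estimate an SD for a later phase III trial, so no promised figure is falsified.

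It also stands that the gain depends wholly on assumed values and is only about 4 points at correlation 0.3.

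**Conclusion.** The point holds as one of consistency and efficiency. The endpoint sentence and the test describe different quantities, and the test leaves freely available precision unused. Under the stated assumptions, baseline adjustment raises power from 55% to between 59% and 83%, a gain of roughly 4 to 28 points across correlations 0.3 to 0.7. The size is illustrative because the article supplies neither effect nor correlation. The direction is firmer: adjustment reduces the variance at any non-zero correlation, at the price of one degree of freedom. Simply matching the test to the endpoint sentence with a change-score t test would cost power below correlation 0.5. Since the planned test is valid and the conflict lies in a single sentence, this is a should-fix.

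**What to change.** In both the Primary outcome and Statistical analysis sections, name one primary analysis: the XBYRT minus placebo difference in GHS at week 8, estimated by ANCOVA with arm and baseline GHS as the only terms, reported with its 95% CI. Reword the endpoint sentence as GHS at week 8, adjusted for baseline GHS.

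Keep the unadjusted t test and the linear mixed model as supportive. The mixed model should not be left as an alternative primary: with dropout it draws on a different set of observations from a week 8 ANCOVA, and its clinically relevant factors are not named in the article. Offering both would again leave the primary result open.

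The cost is a wording amendment to the approved protocol of a recruiting trial, made before unblinding. No visits, data or patients are added, because baseline GHS is already collected.

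### Each biomarker gets an unadjusted t test beside a baseline-adjusted mixed model with neither governing, and mtDNA is compared as an exponentiated copy number, which can cost power

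*Protocol article*

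**What the plan says.** All references are to the protocol article.

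- **Statistical analysis.** "Biomarker levels will also be evaluated using" t tests and linear mixed models. The mixed model is described just before this as "adjusting for baseline values and clinically relevant factors", with individual effects as random. The t test is described without adjustment. No order of precedence is given.
- **Mitochondrial DNA content.** ΔCt is the nuclear Ct minus the mitochondrial Ct. The section then goes one step further: "The relative mtDNA copy number is derived from 2 × 2^ΔCt^, taking into account that nDNA is diploid".
- **Outcomes, Biomarkers.** For the inflammatory markers the comparison is of "Changes in circulating levels of inflammatory markers CRP, TNF-α, IL-1β, IL-6 and IL-8 from baseline to 4, 8 and 10 weeks". Oxidative stress markers and mtDNA levels are compared between arms at the same visits.
- **Inflammatory cytokines.** "The cytokines of interest will be quantified using the highly sensitive multiplex immunoassay". No SD, distribution or effect size is given for any marker, and no transformation is mentioned.

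**The concern.** There are two separate weaknesses.

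First, two methods are fixed for every marker. They target the same question with different precision and can disagree. The variable is also described in two ways: Statistical analysis speaks of levels, while Outcomes speaks of changes for the inflammatory markers. With no governing analysis, the choice of which result to report stays open until after the data are seen.

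Second, the plan computes ΔCt, on which Ct errors are additive, and then exponentiates it before the comparison. Symmetric variation in ΔCt becomes right-skewed variation in copy number. If the concentrations are also right-skewed and analysed untransformed, the same loss applies to them.

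What is at stake is power for the mechanistic results. The Discussion relies on these markers as an objective view of response, from about 35 evaluable participants per arm.

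**Working it through.** **The plan's own figure.** Sample size gives 70 evaluable (35 per arm) and 10% dropout: 70 / 0.9 = 77.8, so 78, rounded up to 80. This reproduces. It is not a biomarker power calculation, and the article contains none. With 80 randomized and 10% lost, 80 × 0.9 = 72 remain, or 36 per arm.

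**Number of analyses.** There are nine markers (CRP, TNF-α, IL-1β, IL-6, IL-8, MDA, SOD, GSH-Px, mtDNA) and three follow-up visits: 9 × 3 = 27 comparisons. If both methods are run at each visit, 27 × 2 = 54.

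**The mtDNA variable.** If copy number = 2 × 2^ΔCt, then log2(copy number) = 1 + ΔCt. Analysing ΔCt is therefore the same as analysing the log of copy number, and a between-arm difference d in ΔCt is a geometric mean ratio of 2^d. The natural-log SD of copy number is 0.693 × SD(ΔCt):

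- SD 0.3 cycles: 0.693 × 0.3 = 0.21
- SD 0.5 cycles: 0.693 × 0.5 = 0.35
- SD 1.0 cycle: 0.693 × 1.0 = 0.69

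These SDs in cycles are assumptions.

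**Power when the log-scale SD is large.** Simulation with assumed inputs: lognormal values, 36 per arm, true ratio 0.6 (a 40% reduction), baseline correlation 0.6, two-sided 5%. The mixed model is represented by baseline-adjusted analysis of covariance at one visit.

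| Log-scale SD | t test, untransformed | t test, logs | Baseline-adjusted, untransformed | Baseline-adjusted, logs |
|---|---|---|---|---|
| 0.7 | 76% | 85% | 89% | 96% |
| 1.0 | 41% | 58% | 53% | 76% |
| 1.3 | 22% | 38% | 27% | 53% |

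Repeat runs agree to within about 2 points. The two components of the gain separate as follows:

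- Baseline adjustment alone, untransformed: 89 − 76 = 13, 53 − 41 = 12 and 27 − 22 = 5 points.
- Log scale, given baseline adjustment: 96 − 89 = 7, 76 − 53 = 23 and 53 − 27 = 26 points.

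An untransformed t test on change from baseline, the quantity named for the inflammatory markers, has 69, 32 and 16% under the same assumptions.

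**Power when the log-scale SD is small.** A second simulation used 35 per arm and a log-scale shift of 0.68 SD, chosen so that the log-scale t test has about 80% power. For the t test on levels, logs versus untransformed:

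- SD 0.2: 80% v 79%
- SD 0.3: 80% v 79%
- SD 0.5: 80% v 75%
- SD 0.7: 80% v 71%

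For mtDNA, a spread of 0.3 to 0.5 cycles thus costs about 1 to 3 points (interpolating at the upper end), and a spread of 1 cycle about 9 points.

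**Type I error.** Across the simulated settings it is about 3.4 to 5.4%. The untransformed test is valid and becomes slightly conservative at high skew.

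**The case against.** The strongest reply is that the article never names a scale. t tests and linear mixed models are equally the tools for logged values or ΔCt, and transformation of laboratory markers is commonly left to an analysis plan that is not shown. Cytokine skewness is not in the article either. This stands for the concentrations. A reader might infer that the plan commits to untransformed tests on skewed cytokines, but the document supports neither half of that. For mtDNA the reply is weaker: the article defines copy number as the derived measure and then compares mtDNA levels, and the plain reading is that the exponentiated value is tested.

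A second reply is that the plan already contains a baseline-adjusted model, so setting 96, 76 and 53% against the unadjusted t test credits the log scale with gains that the plan partly has. This also stands. The like-for-like contrast is 89 v 96%, 53 v 76% and 27 v 53%. It does not answer the missing precedence: the t test remains a named analysis.

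A third reply is that a reader might infer false positives driven by outliers. The type I error figures do not support that. The only cost is power, and it is material only if the log-scale SD is large.

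**Conclusion.** The point holds in limited form and is of low severity. Two things rest on the document alone: two analyses per marker with none governing, and an mtDNA variable exponentiated before comparison. For the concentrations, the most that can be said is that no transformation is stated.

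The size is conditional on marker SDs that the article does not give. At log-scale SDs of 0.7 to 1.3, under the stated assumptions, keeping the untransformed scale costs a baseline-adjusted analysis about 7 to 26 points of power. At 0.35 or below, for levels, the cost is about 1 to 3 points, which is negligible. It would be too strong to say that real biomarker effects will be missed, or that mtDNA in particular is badly served: if ΔCt varies by 0.3 to 0.5 cycles, little is lost. Biomarkers stand apart from the primary and secondary outcomes and carry no power claim, so the trial's main conclusions are unaffected.

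**What to change.** Drop the biomarker t tests and make the baseline-adjusted linear mixed model the single analysis for each marker. Analyse mtDNA as ΔCt. Log-transform CRP and the cytokines, and the oxidative stress markers if they prove skewed. Report geometric mean ratios with 95% confidence intervals.

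Suggested wording: *Each biomarker is compared between arms by one linear mixed model adjusted for its baseline value. CRP and cytokines are log-transformed and mtDNA is analysed as ΔCt; oxidative stress markers are log-transformed if skewed. Results are given as geometric mean ratios with 95% CI for markers analysed on a log scale or as ΔCt.*

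The cost is a short text change, with no new data or visits. The small downside is that results are ratios rather than absolute differences. How to treat values below the assay limit is optional detail for the SAP and is not part of this point.
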